## Methods

### Study Design and Setting

This nonrandomized, exploratory, observational case-control study integrates the concept of TCM diagnostic methods with contemporary tools in an effort to provide an unbiased perspective on the syndrome differentiation of patients with diabetes and those with prediabetes, and, as a result, provide a guideline for the treatment options specifically targeted at the local population.

The research will be conducted between September 2022 and April 2025 at the Singapore Chung Hwa Medical Institution after obtaining approval from the Parkway Independent Ethics Committee (PIEC; reference: PIEC/2022/003). This study is registered under ClinicalTrials.gov (NCT05563090). Figure 3 depicts the study flow diagram.

**Figure 3 figure3:**
[figure not shown]
The study flow diagram. DIA: diabetes without hypertension or dyslipidemia; DIAHD: diabetes with hypertension and dyslipidemia; HEA: healthy or subhealthy; PRE: prediabetes without hypertension or dyslipidemia; PREHD: prediabetes with hypertension and dyslipidemia; TCM: traditional Chinese medicine.

### Recruitment of Participants

To ensure a sufficient sample size for statistical analysis of the diabetic and prediabetic syndrome differentiation, we intend to recruit 250 participants who will be equally assigned to one of 5 arms. The groups are as follows: group 0: healthy or subhealthy without diabetes, hypertension, or dyslipidemia; group 1: prediabetes without hypertension or dyslipidemia; group 2: diabetes without hypertension or dyslipidemia; group 3: prediabetes with hypertension and dyslipidemia; and group 4: diabetes with hypertension and dyslipidemia. Primarily, recruitment is conducted through physician referrals, as well as recruitment posters on the institution’s bulletin boards and social media. Participants can register through the digital registration form, while the screening and enrollment will be conducted by the study team. The list of potential participants will be consolidated, and the research assistant will contact the participants to guide them through the informed consent process. Written consent will be collected when informed consent has been explained to the participant in a language they can comprehend. The participants will have the opportunity to decline enrollment at any time, and they are not required to present a justification for doing so. A study ID based on the grouping will be assigned after screening and enrollment according to the inclusion and exclusion criteria. The first 50 participants who qualify for each of the 5 groups and complete the screening process will be included, and recruitment for that particular group will cease once the target number is reached. This ensures that each of the 5 groups has an equal number of participants, allowing for balanced and effective statistical analysis.

Enrollment criteria include: (1) demographic: aged 21-75 years, of any sex or race; (2) clinical conditions include diabetes that have been clinically diagnosed by Western medical professionals (FPG7.0 mmol/L, 2-hour plasma glucose [2hPG]11.1 mmol, or HbA_1c_>6.5%) with or without hypertension and dyslipidemia, prediabetes that have been clinically diagnosed (impaired fasting glucose of FPG 6.1-6.9 mmol/L or impaired glucose tolerance with 2hPG of 7.8-11.0 mmol/L); and (3) control group consists of participants who are healthy or subhealthy and do not have any significant health-related issues, such as clinically diagnosed chronic conditions like diabetes, hypertension, or dyslipidemia. The health evaluation form will be used to confirm that they (1) do not have a family history of diabetes and (2) have not had unusually high FPG levels detected within the last year.

Participants with the following conditions will be excluded from our study: (1) gestational diabetes; (2) pregnant or lactating women; (3) chronic heart failure, carcinomas undergoing chemotherapy, and psychological or psychiatric disorders; (4) heart diseases and transplanted devices such as pacemakers; (5) acute infections such as upper respiratory infections, acute gastroenteritis, or urinary tract infections; (6) unable to undergo evaluation with the pulse sphygmograph, tongue detection, or complete the questionnaire; (7) communication disorders; (8) gastroenterology diseases or diagnosed with “spleen and stomach deficiency syndrome” by TCM physician; and (9) undergoing TCM treatment for diabetes or prediabetes within 1 week.

To protect the confidentiality of personal information, a unique identifier will be used. The principal investigator will maintain a list of study participants and their identification codes.

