### Sample Size Calculation

In an earlier 3-arm study to investigate the relationship between dyspepsia and rhinitis conducted by Huang et al [44] with 42 participants assigned to each group, there was a significant difference in the high-frequency pulse SE (SE_13-50Hz_) between the control and experimental groups. Huang et al [45] also compared the radial pulse wave characteristics of hypertensive patients against healthy individuals with 46 patients in each group using the same device. Other investigations using the pulse tonometric device indicated a sample size of 25 with an expectation of 5% type 1 error, 80% power, and 5% drop rates based on the mean and SD derived from a study conducted by Huang et al [46,47]. Although there is limited prior data on the investigation of syndrome differentiation and pulse diagnosis of diabetes and prediabetes, we anticipate that a sample size of 50 in each group will provide adequate power to detect statistical significance.

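### Controls are screened for any significant chronic illness and the case groups are not, so group-versus-control differences may partly reflect other disease; the two descriptions of an eligible control also need reconciling

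*Protocol article*

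**What the plan says.** All eligibility text is in the protocol article, Methods, Recruitment of Participants.

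- **Controls, enrollment criteria.** Group 0 participants must be healthy or subhealthy and "do not have any significant health-related issues, such as clinically diagnosed chronic conditions like diabetes, hypertension, or dyslipidemia". The three diseases are given as examples of a wider class. The health evaluation form is also used to confirm that they "do not have a family history of diabetes and (2) have not had unusually high FPG levels detected within the last year".
- **Controls, group list.** Group 0 is defined there by the absence of three named diseases: diabetes, hypertension and dyslipidemia. No other condition is mentioned.
- **Cases, group list.** "group 1: prediabetes without hypertension or dyslipidemia" and "group 2: diabetes without hypertension or dyslipidemia"; groups 3 and 4 are the same glycemic categories with both comorbidities. Other chronic illness is not mentioned for any of the four.
- **Exclusions for all groups.** These include "chronic heart failure, carcinomas undergoing chemotherapy, and psychological or psychiatric disorders", heart disease and implanted devices, acute infections, and "gastroenterology diseases or diagnosed with “spleen and stomach deficiency syndrome” by TCM physician".

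Statistical Analyses compares SE13-50Hz in each group with control by ANOVA. The ANCOVA names gender, age, BMI and physical activity and then leaves the covariate list open.

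Sample Size Calculation cites a 3-arm study "to investigate the relationship between dyspepsia and rhinitis" in which "there was a significant difference in the high-frequency pulse SE (SE_13-50Hz_) between the control and experimental groups".

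**The concern.** A comparison with controls isolates diabetes only if the two sides differ in diabetes and are otherwise selected alike. Under the enrollment criteria they are not. A person with asthma, thyroid disease, arthritis or chronic rhinitis is barred from group 0, or at best doubtful there, but is admissible to groups 1-4.

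The protocol does not treat SE13-50Hz as specific to diabetes. It plans the study from work on other conditions, and under Sufficient Sample Size it describes hypertension, dyspepsia and rhinitis as chronic conditions studied with the pulse device.

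The healthy-versus-diabetes hypothesis for SE13-50Hz is directly exposed, as are the constitution and tongue comparisons with control. A difference caused by general ill health would be reported as a feature of diabetes or prediabetes. The Syndrome Differentiation section relies on standardized devices to minimize bias, but a device measures a badly matched group as faithfully as a well matched one.

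**Working it through.** **1. Who may enter, by group**

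| Condition | Group 0, enrollment criteria | Group 0, group list | Groups 1-4 |
|---|---|---|---|
| Heart disease, cancer on chemotherapy, psychiatric disorder, acute infection, gastroenterology disease | Excluded | Excluded | Excluded |
| Hypertension, dyslipidemia | Excluded | Excluded | Set by group |
| Other diagnosed chronic condition (for example chronic rhinitis, asthma, thyroid disease, arthritis) | Excluded if significant | Not addressed | Not addressed |

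The last row is the issue. Columns two and three disagree, and only column two creates an asymmetry with the cases. Dyspepsia is plausibly removed from every group by the gastroenterology exclusion; rhinitis is not.

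**2. Is there a figure in the plan to reproduce?** No. The article gives no effect size or SD for SE13-50Hz, and no frequency of other illness in any group. The bias can only be scaled under assumptions.

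**3. Scaling the bias**

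Inputs:
- n = 50 per group (Sample Size Calculation)
- two-sided 5% level (Statistical Analyses)
- assumed share of a case group with another condition: 0.20 to 0.40
- assumed shift in SE13-50Hz from that condition: 0.3 to 0.5 SD
- assumed share in controls: 0

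Spurious difference = (share in cases − share in controls) × shift:
- low: (0.20 − 0) × 0.3 = 0.06 SD
- high: (0.40 − 0) × 0.5 = 0.20 SD

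Standard error of a two-group difference = √(2/50) = 0.20 SD. The bias is therefore 0.3 to 1.0 standard errors.

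Chance of P<.05 with no diabetes effect, where b is the bias in standard errors: Φ(b − 1.96) + Φ(−b − 1.96).
- b = 0.3: Φ(−1.66) + Φ(−2.26) = 0.048 + 0.012 = about 6%
- b = 1.0: Φ(−0.96) + Φ(−2.96) = 0.169 + 0.002 = about 17%

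With Bonferroni over the four control comparisons (0.05/4 = 0.0125), the 0.20 SD case gives about 6.7% against a nominal 1.25%. For scale, 50 per group has 80% power for 0.56 SD at the 5% level.

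**4. If controls are not free of such illness.** The bias depends on the gap between groups. If other illness were half as common in controls as in cases, the range would halve to 0.03-0.10 SD.

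**The case against.** The strongest reply is that the control bar is softer than it first reads. The group list gives a closed set of three diseases, subhealthy people are admitted, and only significant issues disqualify. Mild chronic rhinitis may not be barred at all. This stands. It makes the assumed zero share in controls an upper-end case, and it means the asymmetry largely disappears if the group list is the working rule. But the article then gives two different definitions of an eligible control, which must be settled in any event.

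Second, handling is partly in place. The shared exclusions narrow the gap, Health Evaluation records health status, symptoms and Western and Chinese medications, and the open covariate list could take in comorbidity. An analysis plan not shown may name it. That is fair, and an unnamed covariate is not faulted here. The point rests on the two printed sets of criteria, which do differ. An open list does not commit to handling that difference.

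Third, a healthy comparator is a defensible choice in an exploratory study, and 140 of 250 participants were already enrolled by July 15, 2024. Changing case eligibility now would mix two populations within a group. This also stands, and the fix avoids it.

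Three stronger readings are tempting and not supported:
- **That rhinitis is shown to alter SE13-50Hz.** The article reports a difference between control and experimental groups in a study of dyspepsia and rhinitis, without saying which arm differed, by how much, or in which direction.
- **That groups 1 and 2 are promised as diabetes or prediabetes in isolation.** They are described only as lacking hypertension and dyslipidemia.
- **That false positives would be frequent.** A rate of about 65%-70% needs half the cases affected and a shift of 1.0 SD; nothing in the article supports either value.

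**Conclusion.** The concern holds conditionally. If the enrollment criteria are the rule applied, every group-versus-control contrast sets people screened for other chronic illness against people who were not, and part of any difference may not belong to diabetes or prediabetes.

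Its size cannot be derived from the article. The 0.06-0.20 SD range rests wholly on the assumed frequency and shift, and on no such illness in controls. At most it equals one standard error of a two-group difference at 50 per group. It could be negligible, but the criteria do not bound it.

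Comparisons among groups 1-4 are untouched by the control rule. This is a modest point of interpretation that is cheap to address. It does not invalidate the design.

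**What to change.** 1. **Reconcile the two control definitions.** State in one place whether a diagnosed chronic condition other than diabetes, hypertension or dyslipidemia bars entry to group 0, and which rule has been applied to controls already enrolled.
2. **Prespecify a sensitivity analysis.** Repeat the group-versus-control comparisons of SE13-50Hz and constitution in participants of all five groups without other diagnosed chronic conditions. Set aside the group-defining conditions and diabetes complications, so that cases are not stripped of their own disease. Identify these participants from the health status and medications recorded under Health Evaluation, ideally by someone unaware of the pulse and constitution results.
3. **Report it beside the main result.** Compare the estimated differences and their intervals, not whether each crosses P<.05. Limit attribution to diabetes if the two analyses differ.

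No mid-study change of case eligibility is needed.

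**Cost.** No new data are required, only classification of records already held. The price is precision. If 20%-40% of a case group were set aside (assumed) and all 50 controls kept, 40 to 30 cases would remain. The standard error would rise from 0.20 SD to √(1/40 + 1/50) = 0.21 SD or √(1/30 + 1/50) = 0.23 SD, giving intervals about 6% to 15% wider.

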### Current Possible Gaps in Syndrome Classification of Diseases

It should be noted that the syndrome classification was developed using China’s demographic data. We speculatively believe that this could be notably dissimilar from countries with tropical climates like Singapore due to the region’s specific geographical and meteorological characteristics. Local research on the body constitution of a multiracial population revealed that qi-deficiency, phlegm dampness, and damp heat were the 3 most prevalent conditions [28]. Another local study reported a significant difference in the syndrome differentiation of knee osteoarthritis, wherein a much higher proportion (51%) of these patients experience spleen and kidney deficiencies with dampness syndrome compared to only 4.2% of those in China [29].

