### Specific Aims and Hypothesis

This study aims to identify the gap in syndrome differentiation between the subjective and objective TCM diagnosis. We devised a protocol for a nonrandomized, exploratory, observational case-control study with equal allocations in 5 arms to investigate the syndrome differentiation of diabetes and prediabetes. We hypothesize that the local TCM syndrome differentiation of diabetes and prediabetes in the tropical climate may differ from that defined based on the Chinese demographic. We also speculate that the high-frequency spectral energy (SE_13-50Hz_) may reflect a difference in pulse wave intensity and density between the healthy and diabetes groups. We will validate the syndrome differentiation using contemporary technologies such as the tongue imaging device and the pulse sphygmograph. An objective diagnosis of the tongue could be achieved with the advancement of artificial intelligence and imaging technology [36,37]. Images of the tongue captured with the tongue diagnostic device will then be processed through an algorithm for comparison and analysis against standard tongue diagnosis images (Figure 2). Furthermore, the development of pulse sphygmographs has enabled the digitalization of pulse assessment. Researchers investigated quantitative analyses of pulse profiles in the time and frequency domains [30]. The development of these quantitative and graphical representations of the pulse profiles in the 6-pulse positions is a significant step toward transforming traditional pulse diagnoses into scientific and objective assessments (Figure 1) [31].

The objective assessment will potentially increase the accuracy of the identification, diagnosis, and prevention of diabetes and prediabetes through a targeted treatment system tailored to the local population.

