#### Pulse Sphygmograph

The Asia Plus Pen Pulse Analysis System Model PPAS-93 (Asia Plus Biotech Co, Ltd) will be used to identify pulse profiles.

The PPAS-93 is a noninvasive device that comprises a high-precision pressure sensor pen and a pulse analyzer. The high-precision pressure sensor pen is a portable handheld pen that digitalizes the biological signal of the radial pressure pulse wave and provides graphical analysis using fast Fourier transformation. This electronic gadget incorporates a high-precision pressure sensor, a filter, an amplifier, and a signal recording card connected to signal analysis software. The sampling rate is 3000 Hz, and the frequency response is between 0.1 and 50 Hz.

With the participant sitting in a relaxed position, the *cun, guan,* and *chi* pulses of each hand will be assessed using the sensor pen with appropriate vertical pressure. The result will be recorded when the best spectrogram displays the highest amplitude. A summation of SE in the 0-10 Hz (SE_0-10Hz_), 10-50 Hz (SE_10-50Hz_), and 13-50 Hz (SE_13-50Hz_) frequency ranges will be obtained. Figure 1 depicts the pulse sphygmograph and its application output.

The time domain analysis examines the amplitude and shape of the arterial waveform such as surging, slippery, fine, and thready [30]. The pulse rate per minute can be determined by the number of waves in 6 seconds multiplied by 10. This will determine the rate such as a rapid or slow pulse. The frequency domain analyzes the variation of SE in the radial pulse waves [30]. The quantitative measures can assess the intensity and density of the SE, providing insight into the deficiency, repletion, coldness, heat, or dampness syndrome. An in-depth examination of both the time and frequency domains will be conducted to deduce the associated syndrome-etiology differentiation of *xiao-ke* (Table 2).

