#### Syndrome Differentiation

The syndrome differentiation of *xiao-ke* will be based on the objective assessment results analyzed from CCMQ, tongue, and pulse diagnosis regardless of the participants’ group status. Data collection under standardized conditions using contemporary diagnostic devices is expected to enhance stability and reliability in syndrome differentiation. This approach effectively minimizes bias and eliminates the necessity for blinding in our study design.

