## Discussion

### Expected Findings

We anticipate that diabetes and prediabetes with or without hypertension and dyslipidemia would have different body constitutions compared to healthy individuals. The prevalence of specific TCM syndrome differentiation may be more common in countries with hot and humid tropical climates, albeit it may differ from the Chinese demographic.

TCM diagnosis is a comprehensive approach that integrates observation, inquiry, pulse palpation, and tongue diagnosis. Finger sensitivity required for palpating radial pulses and precise visual assessment of the tongue are fundamental to accurately detecting variations in the pulse and tongue quality in TCM diagnosis. However, traditional methods of syndrome differentiation are highly subjective and skill dependent. The interpretation of pulse quality and tongue characteristics can differ across practitioners based on their clinical training, experience, and personal bias. This may result in observations lacking clinical significance. To mitigate subjectivity and provide impartial evaluations, we designed this protocol to examine the syndrome differentiation of patients with diabetes and those with prediabetes using contemporary TCM diagnostic technologies. The data collected and evaluated under standardized conditions using these contemporary diagnostic devices are expected to yield stable and unbiased results. This standardized assessment will facilitate more consistent and reliable syndrome differentiation, which is crucial for both clinical practice and research. Thus, our findings may enhance the accuracy of the identification, diagnosis, treatment, and prevention of diabetes and prediabetes through targeted approaches, potentially improving patient outcomes and management effectiveness. Additionally, we will explore and analyze the correlation between TCM syndrome differentiation and WHO diagnosis criteria for diabetes. Establishing the reliability of contemporary TCM diagnostic tools sets the stage for their broader adoption in clinical practice and enables future research into individualized treatment plans based on objective TCM syndrome differentiation. Some of the following study challenges are expected.

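### Exclusion 8 screens out a TCM syndrome although the first hypothesis is about the local distribution of TCM syndromes, so that syndrome is under-counted

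*Protocol article*

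**What the plan says.** Exclusion 8 (Protocol article, Recruitment of Participants) has two halves: gastroenterology disease, and a TCM physician's diagnosis of "spleen and stomach deficiency syndrome". It applies to all five groups. The article gives no reason for the second half and does not say whether the diagnosis must predate the study or can be made at screening.

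The aim (Specific Aims and Hypothesis) is "to investigate the syndrome differentiation of diabetes and prediabetes", and the first hypothesis is that "the local TCM syndrome differentiation of diabetes and prediabetes in the tropical climate may differ from that defined based on the Chinese demographic". Expected Findings adds that the "prevalence of specific TCM syndrome differentiation may be more common in countries with hot and humid tropical climates".

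The study's own syndrome assignment comes after enrolment. Under Syndrome Differentiation, it "will be based on the objective assessment results analyzed from CCMQ, tongue, and pulse diagnosis regardless of the participants", that is, whatever group they are in.

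As background, the section on gaps in syndrome classification cites a local knee osteoarthritis study in which "a much higher proportion (51%) of these patients experience spleen and kidney deficiencies with dampness syndrome compared to only 4.2% of those in China". The section on conventional TCM techniques says that diagnosis resting only on the practitioner's judgement, touch and sight can be inconsistent.

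**The concern.** A study that describes how a population divides among syndromes should not use one of those syndromes to decide who enters. Here, people carrying one named syndrome are turned away before the CCMQ, tongue and pulse assessments are made. They leave no outcome data, so no later analysis can recover them.

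Three things are at stake.

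- **The local distribution.** The excluded syndrome is seen less often than it occurs, and every other syndrome looks more common than it is.
- **The comparison with China.** A local pattern that has been truncated at entry is not comparable with a published pattern that has not.
- **The contrasts between groups.** Having such a diagnosis requires contact with a TCM physician. If that contact differs between healthy volunteers and people with diabetes or prediabetes, the truncation differs too. Applying the same rule to all groups does not prevent this.

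The criterion also brings back, at entry, the practitioner judgement that the instruments are meant to replace.

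**Working it through.** The plan has no figure of its own to reproduce here. It states no syndrome prevalence and no expected number of exclusions. The 50 per group under Sample Size Calculation does not bear on this point.

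**Inputs**
- p, the true share of the source population with the excluded syndrome: not in the article, so assumed. The range 4.2% to 51% borrows the two figures of the knee osteoarthritis study as arbitrary end points only. They concern a different disease and a different syndrome.
- e, the share of those people who carry the diagnosis and are therefore excluded: not in the article, assumed 25% to 100%.
- Simplifications: one syndrome per person, and the practitioner's diagnosis falls only on people who have the syndrome. The article states neither.

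**Formula.** Of N people in the source population, pN have the syndrome and peN are excluded. N(1 − pe) remain, of whom p(1 − e)N have the syndrome. Hence:
- observed share of the excluded syndrome = p(1 − e)/(1 − pe)
- each other syndrome's share is multiplied by 1/(1 − pe)

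For p = 20% and e = 25%, the observed share is 0.20 × 0.75/(1 − 0.05) = 0.15/0.95 = 15.8%, and the multiplier is 1/0.95 = 1.05.

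**Results** (observed share, then multiplier for other syndromes)

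| p | e = 25% | e = 50% | e = 75% | e = 100% |
|---|---|---|---|---|
| 4.2% | 3.2%, 1.01 | 2.1%, 1.02 | 1.1%, 1.03 | 0%, 1.04 |
| 20% | 15.8%, 1.05 | 11.1%, 1.11 | 5.9%, 1.18 | 0%, 1.25 |
| 51% | 43.8%, 1.15 | 34.2%, 1.34 | 20.6%, 1.62 | 0%, 2.04 |

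**Between groups.** Suppose that two groups have the same true prevalence of 20%, but e is 25% in one and 75% in the other. The observed shares are 15.8% and 5.9%. That is a difference of 9.9 percentage points produced by the entry rule alone.

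Sample size does not enter either formula. More participants would narrow the interval around the wrong value.

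**The case against.** The strongest case on the other side has four parts.

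1. *The exclusion and the outcome are different variables.* One is a physician's diagnosis. The other is assigned from CCMQ, tongue and pulse, and spleen and stomach deficiency is not one of the five classes in Table 2. This stands as a limit on size: truncation may be only partial. It does not remove the problem, because the hypothesis is precisely that local syndromes may depart from the Chinese classification.

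2. *The criterion may have a purpose.* It is paired with gastroenterology disease, and Sample Size Calculation cites a dyspepsia and rhinitis study in which SE13-50Hz differed between groups. Removing digestive conditions may protect the pulse comparison. That is plausible, but the article does not say it, so a stated reason is a fair request.

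3. *Changing eligibility now has its own bias.* By 15 July 2024, 140 of 250 participants were enrolled, and each group closes at its first 50. Groups that fill at different times would have different mixtures of the two rules, and a full group would have none under the new one. This stands, and it is why deletion is not the main remedy.

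4. *The study calls itself exploratory and a pilot, and Statistical Analyses describes no formal test against China.* This lowers the stakes for error rates. The conclusion that the hypothesis invites would still be affected.

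A reader might also infer that dampness patterns cannot be recorded, or that everyone, controls included, is forced into a Table 2 class. The article does not support this. The CCMQ has phlegm-dampness and damp-heat categories, the pulse section lists dampness among the syndromes it informs, and the tongue system reports its own syndromes. The pulse analysis is used "to deduce the associated syndrome-etiology differentiation of" xiao-ke with reference to Table 2, but nothing says that the table is exhaustive.

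**Conclusion.** The point holds. Followed as written, the plan under-counts one syndrome in a study whose first hypothesis is about how syndromes are distributed locally. The direction is known: down for the excluded syndrome, up for the others taken together. The size is not known. At an assumed prevalence of 20%, the inflation of the other shares runs from 1.05 to 1.25; at 4.2% it is at most 1.04. All these figures rest on the assumed p and e, on one syndrome per person, and on a practitioner's diagnosis that matches the syndrome.

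A reader might take from the 51% figure that the other shares are about doubled (1/0.49 = 2.04). The article does not support that. The figure belongs to spleen and kidney deficiency with dampness in knee osteoarthritis, and the factor also requires that every case is already diagnosed. Distortion of the group contrasts is conditional as well: it arises if prior diagnosis differs by group, which is plausible but not shown.

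The consequence is for what may be concluded. The data can describe people without a diagnosed spleen and stomach deficiency. They cannot describe the local syndrome distribution as a whole.

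**What to change.** 1. **Count.** Record, by group, how many candidates are excluded for this syndrome, separately from gastroenterology disease. The full protocol may already log screen failures; what matters is that these counts reach the report. They are a minimum, since people who are never referred or never register are not seen.

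2. **Sensitivity range.** With x of n participants in a group showing a syndrome and k excluded, report x/(n + k) to (x + k)/(n + k) beside x/n. With invented counts n = 50, x = 5 and k = 5, the observed 10% would sit beside a range of 5/55 = 9.1% to 10/55 = 18.2%.

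3. **Limit the comparison with China.** State it for people without a diagnosed spleen and stomach deficiency, as group-specific proportions with 95% confidence intervals against a named published distribution. Do not attribute differences to climate, because no sample from China is collected.

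4. **State the reason** for the syndrome half of exclusion 8, and whether the diagnosis is prior or made at screening.

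5. **If the sponsor chooses to drop that half,** do so only for groups still open, record the diagnosis as a variable, and show results with and without those participants. The gastroenterology half is not affected.

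The cost of items 1 to 4 is a narrower conclusion and a little more reporting. Item 5 would need an amendment and would leave groups recruited under mixed rules, so it is optional.
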